## Analysis

### Power calculation

In this retrospective study, the sample size is fixed. The Evaluability Assessment estimated around 3000 births in FNP cohorts between 2010 and 2015 and around 6000 in the Controls [24]. This large sample size would permit very precise estimation of overall intervention effects for a primary or co-primary outcomes. However as specified by Scottish Government, there is no pre-specified prioritisation of the short- or medium-term outcomes and as such no power calculation is necessary. 

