#### Controls

In a natural experiment, to enable an unbiased comparison of Cases and Controls, measured risk factors associated with outcomes (known as covariates) should be sufficiently similar (and thus balanced) for both exposure groups. As the potential Controls would have been eligible for enrolment on FNP during a period of non-recruitment, they are already a more homogenous comparison population (according to age, area and parity). It is likely, therefore, that the Controls will be sufficiently similar to Cases. However, a possible threat to an unbiased comparison is the enrolment of mothers into FNP on criteria other than age, area and parity, and balance may not be adequate. For example, if mothers who are approached but not enrolled in FNP differ from those who are enrolled for characteristics that are associated with variation in outcomes, comparisons with all eligible Controls may under- or overestimate any effect of FNP. One way to address this is to match the population further as it may provide a more valid estimate of effects because only women with similar observed characteristics are included. The disadvantages of this approach would be that not all Cases would be matched to Controls, which would risk the exclusion of Cases and reduce the sample size. The approach taken here will retain all Controls and given the possibility of a homogeneous comparison group, results will be more generalizable, and result in higher power.

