### Main analyses

With no primary outcome, equal importance will be given to each short and medium term outcome. All comparative analyses will therefore be exploratory, pre-specified and conducted on an intention to treat (ITT) basis. ITT in this study means that the analysis will include everyone who started the programme, according to their original ‘allocation’, i.e. the intervention group will be women enrolled in FNP regardless of the treatment (intervention) they actually received.

All analyses will compare outcomes (intervention effect) between the two groups (Cases and Controls) using multilevel regression models, to allow for clustering of outcome within NHS HB, and FNP team/cohort (where more than one team runs within a HB). Multiple births will be analysed as separate children and the potential clustering of outcome will not be taken account for in analyses due to the small numbers expected. Intervention effects will also be examined over time and between different geographical areas (HB and team/cohort) by fitting multilevel models and interactions (group x year). Alongside the estimate of effect, for all outcomes a 95% confidence interval (CI) and unadjusted p-value will be presented.

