Binary outcomes will be modelled using a logistic model and presented as odds ratios comparing the odds of an event in a case compared with the Control. For continuous outcomes a multilevel linear model will be fitted and results presented as a difference in means (Case minus Control group). Time to event analyses (e.g. cessation of breastfeeding, time to subsequent birth) will be analysed using a proportional hazards regression model and results presented as hazard ratios. We will ascertain if the proportional hazards assumption has not been violated by inspecting the log (-log(survival)) plot and Schoenfeld residuals. Count data will be analysed using a Poisson multilevel model. If the distribution of events display signs of over dispersion (greater variance than might be expected in a Poisson distribution), then a Negative Binomial model will be used. Results will be presented as the incidence rate ratio in the case arm compared to the Control group. The impact of FNP visits (dosage of intervention) on outcomes will be explored as a sensitivity analysis. Adherence will be defined as the number of FNP visits that a Client received during their programme enrolment overall or by phase (pregnancy, infancy, toddler), dependant on outcome. A number of other sensitivity analyses are proposed including adjustment for any imbalance in confounders (pre-exposure maternal and baby characteristics) (note that these will be assessed for the differing denominators (study populations) dependent on outcome) and adjustment for multiple testing.

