#### Subgroups

We will examine the effect of FNP on pre-specified outcomes by modelling interactions between FNP uptake and pre-specified maternal baseline characteristics such as ever been on the child protection register/ looked after child, substance misuse issues and child demographics such as gender. These analyses are not powered for and will be exploratory in nature. Effect sizes alongside 95% confidence intervals and p-values will be reported.

A detailed statistical analysis plan will be written prior to access to data and signed off by the co-lead for the project. The reporting and presentation of results will be in accordance with the GUILD, STROBE, RECORD and TREND guidelines to ensure the comprehensive reporting of this observational non-randomized evaluation of a public health intervention [31–34]. SPSS and Stata will be used for all analyses [35, 36]. We will adhere to the NSS Statistical Disclosure Control protocol [37, 38]. 

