There are no primary outcomes selected for this evaluation. The implication for this approach is that the large number of statistical tests (34 short- and medium-term proposed in this study) performed will mean that there is an increased risk of finding a significant result by chance (false-positive error) i.e. given a 0.05 alpha there is an 82% (1-0.95^34^) chance that at least one of these tests are statistically significant by chance when the conclusion is not true in the population. Recently, James Heckman and colleagues re-assessed the findings of the Memphis trial of NFP using a ‘step-down’ approach to address multiple significance testing [39]. They concluded that fewer treatment effects survive this more conservative approach but note strong effects surviving, especially for longer term effects amongst boys. For individual studies, other correction methods such as Bonferroni have been suggested but are criticised as being overly conservative. On the other hand, if the sample size is sufficiently large and a moderate number of tests are being carried out, the Bonferroni correction will make little difference to the magnitude of effect sizes that can be detected [40]. The recommendations given by the authors are to report the actual p-values without a correction, and then indicate the number of tests and what the Bonferroni correction threshold would be, allowing the reader to assess the evidence themselves. The more recent trials of FNP including our own (BB:0-2) have taken the standard approach of identifying primary outcomes (in the case of BB:0-2, two primary outcomes per population were assessed) and adjusting the alpha accordingly. In this commissioned service evaluation the proposed analysis are exploratory and results should be interpreted with caution.

There are various governance and contractual requirements placed on this study, many of which were identified and required by the PBPP and/or EAS panel prior to final approval. All researchers have completed the information governance training required by eDRIS to evidence their “approved researcher” status. Thirty-three data sharing and/or data processing agreements were set up between HBs, NSS, NRS, EAS and SG to allow the transfer, processing and storage of data for this study. Setting up the agreements took time and posed a risk to the delivery of the project if HBs didn’t support the work however support was provided by the Scottish Government to facilitate this process. 

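### Confounder adjustment is only an imbalance-driven sensitivity analysis in a non-randomised comparison, so the headline estimates are open to measured confounding

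*Protocol article*

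**What the plan says.** The article describes its design under Subgroups, where the reporting guidelines are meant to secure "comprehensive reporting of this observational non-randomized evaluation of a public health intervention". The Main analyses section says that all Case–Control comparisons are made "using multilevel regression models, to allow for clustering of outcome within NHS HB, and FNP team/cohort". It then gives the model family for binary, continuous, time-to-event and count outcomes, and adds group-by-year interactions to examine change over time. No baseline covariate is named in any of these models.

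Confounders appear at the end of that section: "A number of other sensitivity analyses are proposed including adjustment for any imbalance in confounders". A note adds that imbalance is assessed for the differing study populations, which depend on the outcome.

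Three other places bear on this choice.

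- Under Identification of Cases and Controls, Controls, the article says that "a possible threat to an unbiased comparison is the enrolment of mothers into FNP on criteria other than age, area and parity", that balance may be inadequate, and that the comparison may then under- or overestimate the effect. It declines matching: "The approach taken here will retain all Controls and given the possibility of a homogeneous comparison group".
- Descriptive analysis: Cases and Controls lists baseline covariates chosen in advance for their association with enrolment and outcomes. In that section they are only summarised by group.
- The Discussion accepts that women approached but not enrolled are absent from the Cases, while women like them stay among the Controls. If they differ on measured factors, the bias is to be discussed.

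**The concern.** In a randomised trial an unadjusted main analysis is defensible because allocation protects the comparison. Here enrolment followed an approach and an acceptance, and the article names this as a threat. A variable related to both enrolment and outcome is a candidate confounder by the article's own description, so the natural place for it is the main model.

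Making adjustment depend on observed imbalance adds a second weakness. Confounding bias depends on the imbalance multiplied by the strength of the link with the outcome, so imbalance alone is a poor guide to which variables matter. It also lets the data choose the covariates, and the choice may differ between outcome populations although all short- and medium-term outcomes are given equal importance.

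The reason given against matching is loss of Cases and sample size. Regression adjustment discards no one for lack of a match, so that reason does not count against it.

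At stake is the lead estimate, 95% confidence interval and p-value for every formally analysed outcome. The Conclusions say that the results are to inform policy decisions.

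**Working it through.** **The plan's own error figure.** The Discussion says that "given a 0.05 alpha there is an 82" per cent chance of at least one false positive over 34 tests (25 short-term + 9 medium-term). Check: 1 − 0.95^34 = 0.825, so it reproduces. It assumes that each test has a true 5% error rate, which an unadjusted comparison delivers only if there is no confounding.

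**Inputs from the article.** Group sizes, from Power calculation: "The Evaluability Assessment estimated around 3000 births in FNP cohorts between 2010 and 2015 and around 6000 in the Controls". Of these numbers it says "This large sample size would permit very precise estimation of overall intervention effects". The test level is 0.05, two-sided as implied by the 95% interval.

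**Inputs assumed, because the article gives none.** Outcome rate, size of imbalance and strength of confounding. There is no true FNP effect, and clustering is ignored.

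**Step 1: precision at a 30% outcome.**
SE = √[0.3 × 0.7 × (1/3000 + 1/6000)] = √(0.21 × 0.0005) = 0.01025, or 1.02 percentage points (pp). The 95% half-width is 1.96 × 1.025 = 2.0 pp.

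**Step 2: false-positive rate under a bias b.**
Rate = Φ(−1.96 + b/SE) + Φ(−1.96 − b/SE)

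| Bias b | b/SE | False-positive rate |
|---|---|---|
| 1 pp | 0.98 | 16.4% |
| 2 pp | 1.95 | 49.7% |
| 3 pp | 2.93 | 83.3% |

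For scale, a 10 pp imbalance in a factor that shifts the outcome by 20 pp gives 0.10 × 0.20 = 2 pp.

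**Step 3: a range of confounders.** Take one binary confounder with 30% prevalence in Controls, an outcome risk of 10–30% without it, and a confounder–outcome odds ratio of 2–3. Example: risk 20%, odds ratio 2. The odds with the confounder are 0.25 × 2 = 0.5, so the risk is 0.333. Controls: 0.3 × 0.333 + 0.7 × 0.2 = 0.240. Cases with 40% prevalence: 0.4 × 0.333 + 0.6 × 0.2 = 0.253. The spurious difference is 1.3 pp, the spurious odds ratio 1.07, and the rejection rate of the two-proportion z-test 28.5%. Over the whole range:

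| Imbalance | Spurious odds ratio | False-positive rate per outcome |
|---|---|---|
| 2 points | 1.01–1.02 | 6–8% |
| 5 points | 1.04–1.06 | 9–23% |
| 10 points | 1.07–1.12 | 20–67% |
| 15 points | 1.11–1.19 | 38–95% |

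Correct adjustment for this one confounder in the main model returns the rate to about 5%.

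**What the figures leave out.** Clustering widens the intervals, and the medium-term outcomes rest on a restricted population. For a given bias, both lower the false-positive rates shown.

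**The case against.** The strongest reply is that an adjusted analysis is already planned, so the dispute is about which estimate leads. The article labels all comparisons exploratory, states its aim as association, and discloses the selection problem. Controls meet the same age, first-birth, area and gestation criteria, and Health Board and team are modelled. The article does not list every fixed effect, and a detailed analysis plan is to follow. Inverse probability of treatment weighting is in the abbreviation list, though used nowhere in the text shown.

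Part of this stands. The comparison is restricted by design and structured by area, so calling it simply crude would be unfair. No rule or threshold for imbalance is stated, so the text does not show that any particular confounder would be missed.

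The rest does not remove the point. The article has already given adjustment its role, as a sensitivity analysis, so this is not a detail left to a later plan. The exploratory label concerns strength of inference and multiplicity, and does not reduce bias.

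A reader might also infer three stronger things. One is that the headline estimates are biased and that their intervals will exclude the null through confounding alone. The article gives no imbalance or outcome rate, so this cannot be known. Another is that each of the 34 outcomes gets its own covariate set. The text ties the assessment to study populations, which several outcomes may share. The third is that about 9,000 births underlie every outcome, which the restricted medium-term populations contradict.

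**Conclusion.** The point holds as a criticism of which analysis leads and how its covariates are chosen. By the article's own account selective enrolment is plausible, and suitable covariates were named in advance; yet the main models name none, and adjustment waits on observed imbalance. The headline estimates are open to measured confounding, of unknown direction and size.

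The size rests on assumptions: a 30% outcome, no true effect, no clustering and the full expected sample. Under these, a bias about as large as the interval's half-width (2 pp) makes a nominal 5% test reject about half the time. If the groups are nearly balanced, the effect is slight, as the 2-point row shows.

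Adjustment deals only with what is measured. It would not remove selection on unmeasured factors, including the asymmetry that the Discussion describes.

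**What to change.** In Main analyses, make the covariate-adjusted multilevel model the main analysis for all short- and medium-term outcomes.

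- Use one fixed set of pre-exposure covariates from the baseline table, specified before data access and entered whatever the observed balance. Candidates are deprivation, age at last menstrual period, ethnicity, smoking at booking, body mass index, substance misuse, asthma and mental-health dispensing, previous pregnancy, care and child-protection history, and school history.
- Leave out any variable that FNP could affect. The table's pregnancy-outcome item should be omitted if it refers to the index pregnancy, since the article itself requires covariates unaffected by exposure.
- Report the unadjusted estimate alongside.
- Use propensity weighting on the same covariate set as a sensitivity analysis.
- State that selection on unmeasured factors remains, including the removal of non-enrolled women from Cases only.

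The covariates are already requested, so no new data are needed. The cost is rewording plus a rule for missing covariate values, which linked health, care and school records will make necessary.

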#### Subgroups

We will examine the effect of FNP on pre-specified outcomes by modelling interactions between FNP uptake and pre-specified maternal baseline characteristics such as ever been on the child protection register/ looked after child, substance misuse issues and child demographics such as gender. These analyses are not powered for and will be exploratory in nature. Effect sizes alongside 95% confidence intervals and p-values will be reported.

A detailed statistical analysis plan will be written prior to access to data and signed off by the co-lead for the project. The reporting and presentation of results will be in accordance with the GUILD, STROBE, RECORD and TREND guidelines to ensure the comprehensive reporting of this observational non-randomized evaluation of a public health intervention [31–34]. SPSS and Stata will be used for all analyses [35, 36]. We will adhere to the NSS Statistical Disclosure Control protocol [37, 38]. 

### Study timelines

The study started in July 2016, data will be made available for analysis to begin in January 2020 and will report to the Scottish Government in 2020. 

### Patient and Public Involvement

A lay representative on the study steering committee has provided input on the public facing material describing the study (i.e. lay summary). The PBPP have a number of public representatives contributing to the Tier 2 application review and decision-making.

## Discussion

The study protocol is based upon the specification of FNP commissioned by the Scottish Government. This study design is novel for the evaluation of the FNP/NFP programmes which are primarily evaluated with an RCT. However, assessment of effectiveness in evaluation is limited to outcomes available from routinely collected data. The outcomes for this study have been selected by matching routinely collected administrative data to the Scottish FNP logic model, which is based on the underlying programme theory. Therefore, they have been selected on the basis that they are outcomes FNP aims to influence and there is routine data available to assess the outcome. The Controls are well defined and can be identified from routine data sources. However, one limitation is that women who were approached but not enrolled to the programme were removed from the Cases, but those who might have been approached and subsequently not enrolled will still be present in the control group. Since access to these individuals’ data was not permitted, women of similar characteristics in the Controls cannot be identified to remove them. We can however describe these women who did not take up the programme in a period of recruitment (either not approached or not enrolled) and assess if they are different in any way to the case and control groups. If they are not different on the measured factors, then they do not pose a problem. If they are then the potential bias it might bring to the evaluation will be reflected on in the discussion of the main paper.

There are no primary outcomes selected for this evaluation. The implication for this approach is that the large number of statistical tests (34 short- and medium-term proposed in this study) performed will mean that there is an increased risk of finding a significant result by chance (false-positive error) i.e. given a 0.05 alpha there is an 82% (1-0.95^34^) chance that at least one of these tests are statistically significant by chance when the conclusion is not true in the population. Recently, James Heckman and colleagues re-assessed the findings of the Memphis trial of NFP using a ‘step-down’ approach to address multiple significance testing [39]. They concluded that fewer treatment effects survive this more conservative approach but note strong effects surviving, especially for longer term effects amongst boys. For individual studies, other correction methods such as Bonferroni have been suggested but are criticised as being overly conservative. On the other hand, if the sample size is sufficiently large and a moderate number of tests are being carried out, the Bonferroni correction will make little difference to the magnitude of effect sizes that can be detected [40]. The recommendations given by the authors are to report the actual p-values without a correction, and then indicate the number of tests and what the Bonferroni correction threshold would be, allowing the reader to assess the evidence themselves. The more recent trials of FNP including our own (BB:0-2) have taken the standard approach of identifying primary outcomes (in the case of BB:0-2, two primary outcomes per population were assessed) and adjusting the alpha accordingly. In this commissioned service evaluation the proposed analysis are exploratory and results should be interpreted with caution.

There are various governance and contractual requirements placed on this study, many of which were identified and required by the PBPP and/or EAS panel prior to final approval. All researchers have completed the information governance training required by eDRIS to evidence their “approved researcher” status. Thirty-three data sharing and/or data processing agreements were set up between HBs, NSS, NRS, EAS and SG to allow the transfer, processing and storage of data for this study. Setting up the agreements took time and posed a risk to the delivery of the project if HBs didn’t support the work however support was provided by the Scottish Government to facilitate this process. 

## Conclusions

This is an anonymised data linkage study evaluating the FNP programme in Scotland. It will provide the Scottish Government with indications of the potential effectiveness of this programme in Scotland to contribute to their policy making decisions on early years interventions.

## Declarations

### Ethics approval and consent to participate

South East Scotland Research Ethics Service confirmed the study will not require an NHS Ethical Review as it is a service evaluation.

### Consent for publication

Not Applicable.

### Availability of data and material

Not Applicable.

## Abbreviations

A&E	Accident and Emergency
AGA	Appropriate for gestational age
BB:0-2	Building Blocks Trial
CHI	Community Health Index
CHP	Community Health Partnership
CHSP	Child Health Systems Programme
CI	Confidence Intervals
EAS	Education Analytical Service
eDRIS	Electronic Data Research and Innovation Service
FN	Family Nurse
FNP	Family Nurse Partnership
HB	Health Board
IPTW	Inverse Probability of Treatment Weighting
LMP	Last Menstrual Period
MRC	Medical Research Council
NFP	Nurse Family Partnership
NRS	National Record for Scotland
NSS	NHS National Services Scotland
PBPP	Public Benefit & Privacy Panel
PP	Post-Partum
RCT	Randomised Controlled Trial
SIS	Scottish Information System
SMR	Scottish Morbidity Record
